### Eligibility criteria {10}

#### Objective #1

The study inclusion criteria include: (1) parents with children between birth to 32 months of age (our age ceiling is 36 months, based on selection of age-appropriate tools for assessing children’s health and development); (2) parents who agree to participate in the ATTACH^TM^ program consisting of 10 weeks of additional, concurrent, one-hour per week parent training sessions; (3) parents who agree to bring a co-parent for 2 of the 10 sessions (when possible); (4) parents who agree to the dried blood sample collection to assess immune biomarkers (in Calgary agencies only, due to logistics issue related to blood sample collection, storage, and shipment).

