### Outcomes {12}

Parent-Child Relationship Quality will be measured with the Parent-Child Interaction Teaching Scale (PCITS) [81]. The PCITS is an observational binary measure of relationship quality in an everyday teaching situation, designed for children 36 months or younger. It is considered the gold standard for the assessment of parent-child relationship quality. The PCITS consists of 73 items categorized into six subscales including parental sensitivity to cues, responsiveness to distress, growth fostering, and cognitive growth fostering, child clarity of cues and responsiveness to parent as well as parent total, child total, and parent-child total scores. The scales’ reliability and validity are well established and was observed to be a strong measure of intervention impact in our pilot studies . The observation typically takes 5 minutes to administer and is videotaped to enhance the accuracy of data coding. ATTACH^TM^ interventionists who are health and social service providers in agencies, will be trained to administer the videotaping. Colleagues from the University of Washington will code all videos. During the pilot studies, they retained > 95% intra-rater reliability on 10% of recoded videos and reliable at the 90th percentile with the Canadian study team. Coders are supervised by PI [name] who has been a certified PCITS trainer since 1996 and has kept up annual certification. A protocol for data collection was developed as part of the pilot studies and discussions with patients revealed that the assessment is feasible and acceptable.

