We will employ the Ages and Stages Questionnaire-3rd Edition (ASQ-3) [84] to assess child development in cognitive and motor domains. The cognitive measures include communication, problem solving, and personal-social skills development, while motor measures include both gross and fine motor development. The ASQ-3 is a series of parent-completed questionnaires for age groups ranging from 1 to 66 months, asking six questions in each domain assessing children’s abilities to undertake age-appropriate tasks. Summing items in each domain provides total scores (maximum 60) with higher scores indicating more optimal development; cut-offs are provided to indicate risk for developmental delay in each domain, appropriate to each age group. The ASQ-3 is typically administered in community agencies, thus both agencies and our pilot patients found this measure acceptable and feasible. The ASQ-3 is found to have strong internal consistency reliability (between 0.82–0.88), sensitivity of 86% and a specificity of 85% [85] and is used to identify children at risk for developmental disorder [86].

Dried blood spots (DBS) for assessment of immune biomarkers will be collected by either ATTACH^TM^ interventionists/agency health and social service providers or the research team (agency preference), pre- and post-assessment (only; no 3 month delayed post-intervention assessment), to assay children’s immune cell gene expression (mRNA) [87] and epigenetics (DNA methylation) [88]. DBS collection protocols to reduce distress/discomfort of children were pilot tested with 20 families. While the DBS pilot was optional and parents’ choice, *all children* (*n* = 20) provided blood samples pre- and post-assessment, with minimal distress in children or concerns expressed by parents. Our consultation with agency partners dictates that the DBS will remain optional to avoid deterring patients from participating in ATTACH^TM^. However, our high pilot uptake rate (100%) suggests we will have a sufficient sample. Briefly, a finger is pricked and drops of blood are collected onto specially prepared filter paper cards.

DBS collection is less invasive than traditional venipuncture techniques and is specifically designed for field use [89]. Sex and gender based analysis will also be conducted [90].

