##### ATTACH^TM^ reflective function intervention

The ATTACH^TM^ Reflective Function Intervention can begin after the pre-assessment sessions are completed–usually the following week. ATTACH^TM^ intervention sessions include three components, described above in {11}:

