##### Delayed post-assessment

Three months after the post-assessment data collection is complete, parents will again be asked to evaluate the ongoing effectiveness of ATTACH provide observational, and questionnaire to evaluate the ongoing effectiveness of ATTACH^TM^.

#### Objective 2

NPT interviews will begin as soon as the first family completes the ATTACH^TM^ Reflective Function Intervention Phase and will continue until data saturation is attained, i.e., the degree to which new data repeats or is redundant with what was expressed in previous data [92]. We will employ a stopping rule: Data collection in a category (patient, health and social service providers, and health care administrator) will cease when three interviews in a row offer less than 5% new information (i.e., only one new code to one question of 19 in interview guide offers new information).

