##### **ATTACH**^TM^**impacts**

Every partner agency (including additional agencies) will recruit 2–5 staff members for ATTACH^TM^ training to become the ATTACH^TM^ facilitators. To partake in the ATTACH^TM^ parenting program, participants will be identified through partner agencies. We will intervene with up to 150 parents and their birth to 36-month-old children to retain 100, from 5 community agencies. Parents will be recruited from rosters of patients currently seeking service. The ATTACH^TM^ information sheets and brochures will be posted on implementation sites. Their current and interested clients will be our potential participants. Their staff will assist with recruitment as participants seek their services in routine care.

#### Objective 2

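### The 32-month entry limit keeps the pre- and post-assessments within the PCITS age range, but not the delayed assessment about 5.5 months after entry

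*Protocol article*

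**What the plan says.** Under Eligibility criteria {10}, Objective #1, the entry rule covers "parents with children between birth to 32 months of age (our age ceiling is 36 months, based on selection of age-appropriate tools", so the entry limit and the tool-based ceiling are given in one sentence. Outcomes {12} names the Parent-Child Interaction Teaching Scale (PCITS) as the measure of parent-child relationship quality, the primary outcome, and describes it as "designed for children 36 months or younger".

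The Methods paragraph of the abstract places the PCITS at all three time points, and the delayed post-assessment under Participant timeline {13} includes observational data. The timing is spread over several places:

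- Sessions start after pre-assessment, "usually the following week" (Participant timeline {13}).
- The programme is ten weekly one-hour sessions (Eligibility criteria {10}).
- Post-assessment cannot take place until the programme is complete (Participant timeline {13}).
- The delayed assessment falls "Three months after the post-assessment data collection is complete" (Participant timeline {13}).

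Recruitment {15} speaks of "up to 150 parents and their birth to 36-month-old children", and the abstract gives the same 36-month figure. The ASQ-3, a secondary outcome, is described as "a series of parent-completed questionnaires for age groups ranging from 1 to 66 months". The article gives no rule for a child who passes 36 months before the delayed visit.

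**The concern.** The entry limit appears in the same sentence as the instrument ceiling, so its evident purpose is to keep every child within the age range of the tools for the whole study. A margin of 4 months does that only if the last PCITS falls within 4 months of entry. On the stated schedule it does not.

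At stake is the delayed PCITS for the oldest entrants. It would be the primary instrument used outside the age range that the protocol itself gives for it. Those scores feed objective 1d, the effect at 3 months, and the repeated measures ANOVA across the three assessments in Statistical methods {20a, 20b and 20c}. The children concerned are selected by age, so whatever is done with their scores is not neutral with respect to age. Because the protocol fixes both the entry age and the visit schedule, an analysis plan could only manage the consequence, not remove it.

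**Working it through.** **Inputs**

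- Upper entry age 32 months and ceiling 36 months (Eligibility criteria {10}; Outcomes {12}).
- Lag to first session about 1 week; post-assessment after completion; delayed assessment 3 months after post-assessment (Participant timeline {13}).
- Ten weekly sessions, taken as 10 weeks (Eligibility criteria {10}).
- 1 month = 365.25/12 days = 4.348 weeks.

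**Room allowed by the plan:** 36 − 32 = 4.0 months, or about 17.4 weeks.

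**Room needed**

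- To post-assessment: (1 + 10)/4.348 = 2.53 months.
- To delayed assessment: 2.53 + 3 = 5.53 months.

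**Ages of a child who enters at 32.0 months**

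- Post-assessment: 32 + 2.53 = 34.5 months, inside the ceiling.
- Delayed assessment: 32 + 5.53 = 37.5 months, about 1.5 months past it.

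**Latest entry age that keeps the delayed PCITS in range:** 36 − 5.53 = 30.5 months.

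**Sensitivity to the lags.** The one-week start is described as usual rather than fixed, ten weekly sessions can span nine weeks, and the gap before post-assessment is not given.

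| Start lag, session span, gap before post-assessment | Weeks | Months to delayed visit | Age at post | Age at delayed | Latest entry age |
|---|---|---|---|---|---|
| 0, 9, 0 weeks | 9 | 5.07 | 34.1 | 37.1 | 30.9 |
| 1, 10, 0 weeks | 11 | 5.53 | 34.5 | 37.5 | 30.5 |
| 1, 10, 2 weeks | 13 | 5.99 | 35.0 | 38.0 | 30.0 |

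If the ceiling is read generously, as any age below 37.0 months, the latest entry age rises by one month to between 31.0 and 31.9. A child aged 32.0 months at entry is still beyond it in every row.

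**How many children.** The article gives no age distribution. Assuming entry ages uniform over 0 to 32 months:

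- Central case: (32 − 30.47)/32 = 4.8%, about 5 of 100 families.
- Range: (32 − 30.93)/32 = 3.3% to (32 − 30.01)/32 = 6.2%.
- Generous ceiling: 0.2% to 3.1%.

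**Effect on power.** Sample size {14} gives 100 families and d = .34 for the pre/post difference; alpha is .05 two-tailed. A paired t-test has noncentrality 0.34 × √100 = 3.40 and power 0.92. If the same effect size is carried over to the delayed contrast and 5 pairs are set aside, noncentrality is 0.34 × √95 = 3.31 and power 0.91.

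**The case against.** The strongest reply is that this is small. The sample size is set for the pre/post difference, and under the 32-month limit that contrast stays in range in every variant (34.1 to 35.0 months at post-assessment). What is left is one later time point, for perhaps 5 children in 100, with power moving from 0.92 to 0.91. The criteria permit entry above 30.5 months but do not guarantee that it happens. Narrowing eligibility would also turn away families whose pre/post data would be fully usable. All of this stands. It limits the weight of the point and supports offering a remedy that keeps the 32-month limit. It does not reconcile the margin with the schedule.

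A reader might infer three stronger things that the documents do not support:

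- **That delayed scores past 36 months are invalid, or missing by design.** The article says what ages the PCITS was designed for. It does not say that a score at 37 months is void, and no rule drops such a visit. Age-related missingness would arise only if someone chose to exclude those scores.
- **That the primary contrast is affected, because Recruitment {15} gives 36 months.** If 36 months were the entry limit, a uniform age distribution would put 2.53/36 = 7% over age at post-assessment and 5.53/36 = 15% at the delayed visit. But the eligibility criterion separates entry (32) from ceiling (36), and the recruitment and abstract wording reads more naturally as the ages covered during the study. Those percentages should not be used. The wording is loose enough to deserve alignment.
- **That every analysis of objective 1d needs all three visits.** The plan also lists paired t-tests, which need only the two visits compared.

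**Conclusion.** The point holds, at modest size. The 32-month limit does not do what its stated rationale implies: it protects the pre- and post-assessment PCITS but not the delayed one. A child enrolled above about 30.5 months (30.0 to 30.9 across the variants) can be past the instrument's stated range at the delayed visit, and a 32-month entrant would be about 37.5 months old. The conflict for a 32-month entrant rests only on figures in the protocol and survives every reading of the lags and of the ceiling.

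The reach is limited to objective 1d and any three-wave analysis. The estimate of about 5% of children (3% to 6%) depends on the assumed uniform entry ages; a sample concentrated in infancy would give fewer, and one concentrated in the third year more. Power is not the issue. The issue is a stated limit that misses its purpose, in a trial that is already recruiting.

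A minor related point at the other end of the range: children are admitted from birth but the ASQ-3 forms start at 1 month, so a child who enters before 1 month has no in-range ASQ-3 baseline. On the same uniform assumption that is 1/32, about 3%. The ASQ-3 upper limit of 66 months is not approached.

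**What to change.** Choose one of two routes for further recruitment:

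1. Set the upper entry age, measured at pre-assessment, to about 30 months. This covers the longest schedule variant above (30.0 months). It removes 2/32 = 6.3% of the current age range and needs a short eligibility amendment.
2. Keep 32 months and say plainly that the 36-month ceiling is meant to cover pre- and post-assessment only. This costs no recruitment, but accepts that some delayed PCITS observations will fall outside the instrument's stated range.

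Under either route, and for families already enrolled, record the child's age at each PCITS, flag delayed scores taken after 36 months, and report objective 1d with and without them. A flag with a sensitivity analysis is preferable to dropping those visits from the main analysis, because dropping them would itself create missing data that depend on age.

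State one entry range in the abstract, Eligibility criteria {10} and Recruitment {15}, and keep it distinct from the ages covered during follow-up. Add a sentence that entrants younger than 1 month have no in-range ASQ-3 baseline, or set the lower entry age at 1 month. Beyond the amendment, the cost is a few sentences of text and one additional analysis.

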The voluntary nature of the study will be reinforced verbally throughout the consent process and, indeed, throughout the course of the participant’s involvement in the study. They may choose not to answer some questions asked or to withdraw from the study at any time without affecting their health care or participation in partner agencies’ services. If they choose to no longer participate (at any time including once data analysis has begun), we will retain their data for attrition analyses, unless asked explicitly to remove data from the study, in which case their data collected to date will be destroyed. The interested agencies will approach the potential ATTACH^TM^ participants who are already accessing services at the agencies. Staff at the participating agencies will ensure to avoid any coercion by letting the potentially interested families know that their participation is completely voluntary, and that they can withdraw any time. It will not affect their access to any other services at the agencies if they decide to not participate in the study. To protect the rights of participants, this study will meet the ethical standards set out in the Conjoint Health Research Ethics Board Guidelines refs. A process of informed consent will be implemented, with verbal consent being secured at each stage of the process. In addition to the verbal consent secured during the recruitment and screening process, participants will be provided with a written consent form and will be required to return a signed copy of the written consent form.

We also received ethical approval for an adaptive honorarium schedule of gift cards that provides increased compensation commensurate with increased parent burden. This schedule emerged from numerous collaborative conversations with parents and agency health and social service administrators and providers. The study participants will receive $280 honorarium in total to appreciate them for their time. Additional $100 ($50 × 2 per sampling) will be offered to the families for dried blood sampling collection in the first 80 families in Calgary agencies. Participating agencies will cover the cost for parking and travel, as their typical practice.

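### Agreement to child blood sampling is an entry criterion at Calgary agencies, although the outcomes section says sampling is optional

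*Protocol article*

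**What the plan says.** The protocol article deals with dried blood spot (DBS) sampling in three places that bear on entry.

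- **Eligibility criteria {10}, Objective #1.** The list opens "The study inclusion criteria include: (1) parents with children between birth to 32 months of age" and goes on to agreement to the program. Item (3) is "parents who agree to bring a co-parent for 2 of the 10 sessions (when possible"). Item (4) is "parents who agree to the dried blood sample collection to assess immune biomarkers (in Calgary agencies only"); the stated reason for the geographic limit is sample logistics.
- **Outcomes {12}, Secondary outcomes.** The blood is the child's: it is taken "to assay children’s immune cell gene expression (mRNA") and DNA methylation. On consent: "Our consultation with agency partners dictates that the DBS will remain optional to avoid deterring patients from participating in" ATTACH. On numbers: "our high pilot uptake rate (100%) suggests we will have a sufficient sample". In the pilot, sampling was optional and all 20 children gave samples.
- **Research ethics approval and consent or assent {24 and 26a}.** An extra honorarium is offered for "dried blood sampling collection in the first 80 families in Calgary agencies".

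Objectives {7} names parent-child relationship quality as the primary outcome and gives immune biomarkers their own sub-objective, 1c. Study setting {9} names four initial agencies, three of them in Calgary.

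**The concern.** A Calgary parent who wants the program but refuses a finger prick for the child fails item (4), yet is meant to be welcome under the outcomes section. The document does not say which rule staff should apply.

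The rule reaches beyond the biomarkers. The primary outcome is scored from a short video, and the reflective function and child development measures are questionnaires. None of them needs blood, but the literal criterion would remove decliners from all of them.

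What is at stake is the population. The study aims to show effectiveness in naturalistic community settings and, under Objective 1b, for whom the program works. If willingness to have a child sampled is a condition of entry at the Calgary agencies, the Calgary sample is narrower than those agencies' clientele, and the entry rule differs from that at the Manitoba agency.

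**Working it through.** **1. The two statements side by side.**

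| Question | Eligibility criteria {10} | Outcomes {12} |
|---|---|---|
| Is agreement to DBS needed at Calgary agencies? | Yes, inclusion item (4) | No, optional |
| Is there a qualifier? | By place only | Stated aim is not to deter families |
| Scope | Objective 1 as a whole | The DBS measure |
| May a Calgary decliner enrol? | No, read literally | Yes, by implication |

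Three features make it hard to read item (4) as merely defining the biomarker subset. It stands in the same list as child age and agreement to the program. Its neighbour, item (3), carries a softening term and item (4) does not. Nothing in the article ties it to Objective 1c. In addition, the outcomes section uses voluntary pilot uptake to predict an adequate sample, an argument needed only if families may decline.

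**2. How many families could be affected.** The plan gives no refusal figure for this study, so the pilot is the only input.

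- Pilot uptake (Outcomes {12}): 20 of 20, so observed refusal is 0/20 = 0%.
- Exact two-sided 95% lower limit for uptake: solve p^20 = 0.025, giving p = 0.025^(1/20) = 0.832.
- Upper limit for refusal: 1 − 0.832 = 0.168, about 17%.
- Calgary recruits: 30 per agency (Sample size {14}) × 3 named Calgary agencies = 90. This is an assumption, because Study setting {9} counts four initial agencies while Recruitment {15} counts five.
- Upper bound on families excluded: 0.168 × 90 = 15.1, about 15. At the observed pilot rate the figure is 0.

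**3. Is power affected?** Inputs are 100 completing families and d = .34 (Sample size {14}), with two-sided alpha .05 (Statistical methods). The plan states no power to reproduce.

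- Normal approximation: Φ(0.34 × √100 − 1.96) = Φ(1.44) = 92.5%. The exact paired t-test gives 92.0%.
- Worst case, decliners not replaced: assume a Calgary share of 60% (3 of 5 agencies) to 75% (3 of 4) and 17% refusal. Then n = 100 × (1 − 0.60 × 0.17) = 89.8, down to 100 × (1 − 0.75 × 0.17) = 87.3. Paired t power is 89.0% and 88.1% respectively.
- Sample size {14} says recruitment continues until 100 families complete, so decliners would be replaced and power would stay at about 92%.

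**The case against.** The best defence is that the intended rule is already stated, with its reason: agency partners required sampling to stay optional. On that view item (4) is a loose way of saying who gives blood, the consent forms (Additional files 1 and 2, not shown) may well be right, and with no refusals among 20 pilot families nobody may ever be turned away. It stands that the intention is clear and the number probably small. But the limiting sense is not written anywhere, no text lets a Calgary decliner enrol, and eligibility is core protocol content that staff apply directly.

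Some stronger readings are tempting, and the documents do not support them.

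- **That the honorarium text is a third conflicting rule.** It caps an extra payment at 80 Calgary families. It says nothing about entry and is compatible with optional sampling.
- **That site is confounded with selection in the primary result.** The primary analysis is within-family change in a single group, so each family is its own comparator. Differing entry rules bear on generalisability and, at most, on subgroup contrasts under Objective 1b.
- **That the study loses power or cannot reach its size.** Recruitment continues until 100 families complete, and even without replacement power would be about 88–89%.
- **That biomarker pairs are capped at 3 × 20 = 60.** The 20 families per agency are those retained to the 3-month follow-up, whereas blood is taken only before and directly after the program. The honorarium provides for 80 families.

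**Conclusion.** The contradiction is real and lies between two statements: the eligibility list requires agreement to child blood sampling at Calgary agencies, and the outcomes section makes it optional. Taken as written, the eligibility rule excludes decliners from a primary outcome that needs no blood and selects Calgary families on willingness to be sampled.

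The size is probably small: zero exclusions at the observed pilot rate, and at most about 15 of 90 at the exact 95% limit. That bound assumes 30 recruits at each of three Calgary agencies and a refusal rate like that of the pilot families. The consequence is for who is enrolled and how far the result generalises, not for power or for the validity of the within-family comparison. Severity is moderate: a wrong entry rule that is easy to correct, with a limited expected effect.

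**What to change.** Reconcile the two sections in line with the reason the outcomes section gives:

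- remove item (4) from the inclusion list for Objective 1;
- describe DBS sampling as an optional component offered at Calgary agencies;
- state that refusing it does not affect entry to the program or to the other assessments;
- state that Objective 1c is analysed in children with both a pre and a post sample;
- check that the consent forms say the same. They are not shown, so whether they need any change cannot be judged here.

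The cost is a one-line eligibility amendment, a sentence or two in the outcomes and analysis text, and the consent check. The primary objective loses nothing. Since recruitment began in November 2021, the agencies should also be asked how they have applied the criterion so far.
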